### Methods for additional analyses (e.g. subgroup analyses) {20b}

Logistic regression will be performed for subgroup analysis concerning group assignment, preoperative risk of PONV and administered antiemetic medication and their effects on PONV.

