##### Pharmacological antiemetic prophylaxis

The study aims to identify the effectiveness of P6 acustimulation along with conventional antiemetics administered intraoperatively. Thus, there is a high risk of bias that techniques for P6 stimulation might interfere with the pharmacological measures against PONV and vice versa. Special efforts are undertaken to ensure unbiased and comparable use of antiemetics in both groups. Comprehensive information is provided to the anaesthesiologists which highlight the need for ‘usual care’ in both groups. Additionally, all anaesthesiologists are required to fill in a document for personal ‘self-commitment’. With this form, the anaesthesiologist determines and documents the antiemetic prophylaxis that is suitable and will be administered to the individual patient (for the form, see Additional file 1). This part of the documentation form is filled out and signed by the anaesthesiologist and the attending nurse (four-eyes principle) before group allocation is revealed. This allows the determination of pharmacological interventions against PONV independent of the result of the randomisation procedure.

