##### Antiemetic medication

The anaesthesia staff administers antiemetics according to their self-committed individual medication plan. One of a combination of the following measures may be used:▪ Dexamethasone 4–8 mg▪ 5-HT3-antagonists (e.g. ondansetron 4–8 mg, granisetron 1 mg)▪ Droperidol 0.5–1.5 mg▪ Haloperidol 0.5–1.5 mg▪ Metoclopramide 10–20 mg▪ Dimenhydrinate 50–70 mg▪ Fosaprepitant (no dose restriction)▪ Use of propofol for total intravenous anaesthesia▪Omission of nitrous oxide

The attending anaesthesiologist is free to administer any of the above-mentioned interventions and to combine drugs of different pharmacologic classes (e.g. due to high individual risk of the patient for PONV) but also to withhold antiemetic medication (e.g. if a low risk for PONV is present). Furthermore, the time of administration can be chosen by the overseeing anaesthesia team. The chosen prophylaxis (drug(s), dose, and time of administration) is recorded in a paper-based case report form (CRF).

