##### Intervention

The anaesthesia team is allowed to open the opaque randomisation envelope after completing the self-commitment. This envelope includes information whether the patient is allocated to the control or the intervention group.

Patients allocated to the intervention group receive acustimulation at both forearms at the P6 point immediately after the induction of anaesthesia. Pressure is applied to the needles for about 15 s at the beginning and the end of the intervention to stimulate P6. The applied force should cause the needle tip to reach a depth of 0.5 to 1 cun (traditional Chinese measuring unit) [21]. Anaesthesiologists can also use acupressure bands for intervention instead of acupuncture needles. The intervention and its duration of administration are recorded.

The control group receives only the designated antiemetic prophylaxis according to the self-commitment.

The P6 acupoint is located 2 cun [22] from the distal palmar crease between the flexor carpi radialis tendon and the palmaris longus tendon on the volar surface of both forearms [23]. All anaesthesiologists were informed about the study and were provided with verbal and written information on anatomical location of the P6 stimulation point and the need for applying pressure to the needle. An information sheet (including the illustration from Fig. 1) was available in all operating rooms. For acupuncture, Seirin® New Pyonex needles with a length of 1.5 mm will be used. Acupressure is performed with GoTravel Acustrap bands.

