### Outcomes {12}

#### Primary endpoint

The primary outcome measure for this study is the incidence of PONV within a 24-h observation period. PONV is defined as nausea, retching, vomiting, or the need for any antiemetic medication during the observation period.

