#### Secondary endpoints

Secondary endpoints include the followingThe intensity of PONV during the 24 h observational period is classified using the ‘postoperative nausea and vomiting Intensity Scale’ (PIS) [24],The patient-reported outcome of perioperative quality of life.The incidence and severity of adverse reactions caused by the different combinations of antiemetic drugs.

These endpoints are determined by using the following specific questionnaires:▪ ‘Patient Evaluation in the Perioperative Phase’ (PPP33)▪ Adverse effects via the ‘Postoperative side effects questionnaire’ (PON-F)

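### The additional logistic regression conditions on antiemetics given after allocation is known; the prophylaxis plan signed before allocation should replace them as covariate and subgroup factor

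*Protocol article*

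**What the plan says.** Section {20b} of the protocol article gives the model in one sentence: "Logistic regression will be performed for subgroup analysis concerning group assignment, preoperative risk of PONV and administered antiemetic medication and their effects on PONV".

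Other sections fix when each drug variable comes into being.

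- **Plan.** Under *Pharmacological antiemetic prophylaxis*, the part of the form that holds the intended prophylaxis "is filled out and signed by the anaesthesiologist and the attending nurse (four-eyes principle) before group allocation is revealed". The stated benefit is: "This allows the determination of pharmacological interventions against PONV independent of the result of the randomisation procedure". *Data management {19}* lists the intended prophylaxis among the data collected.
- **Allocation.** Under *Intervention*: "The anaesthesia team is allowed to open the opaque randomisation envelope after completing the self-commitment".
- **Administration.** Under *Antiemetic medication*: "The anaesthesia staff administers antiemetics according to their self-committed individual medication plan". Section {11c} provides for departures from the plan, which are documented with a reason.
- **Endpoint.** "PONV is defined as nausea, retching, vomiting, or the need for any antiemetic medication during the observation period".

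The section on pharmacological prophylaxis also acknowledges a high risk that P6 stimulation and drug measures influence each other. It gives this as the reason for the self-commitment form.

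**The concern.** What a patient is actually given during surgery is settled by staff who know the arm. If some anaesthesiologists withhold a planned drug because P6 is being stimulated, patients with the same administered drugs are no longer alike in the two arms. For example, the P6 patients who received no drug would include some for whom one was planned, while the controls who received no drug would mostly be patients for whom none was intended. A group effect adjusted for administered drugs, or estimated within such subgroups, then compares groups that randomisation did not form.

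A second problem depends on how the term is read. Section {20b} does not confine administered medication to prophylaxis. The PACU section and section {18b} use similar words for drugs given after surgery. Under the endpoint definition a patient who needs such a drug is a PONV case, so including postoperative drugs would put part of the outcome among the predictors.

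At stake are the adjusted and subgroup results, that is, how the P6 effect varies with drug prophylaxis and risk. Apparent drug effects on PONV are also open to confounding by indication, because the article lets anaesthesiologists combine drugs at high risk and withhold them at low risk.

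**Working it through.** The article gives no deviation rate, rescue rate or regression result, so there is no figure of its own to reproduce on this point. The inputs taken from it are 25% against 20% PONV and 1503 patients, read as per arm because 2 × 1750 follows. Everything else below is an assumption.

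**1. Prophylaxis only: simulation.** Logistic regressions were run on 400,000 simulated patients per scenario, under these assumptions:

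- a recorded risk score from 0 to 4 and an unrecorded risk known to the anaesthesiologist, with the chance of a planned drug rising with both (50% planned overall);
- a log odds ratio of −0.6 for a drug that is given;
- planned drugs withheld only in the P6 arm, more often at low unrecorded risk;
- rescue in 60% of patients with symptoms, and a control PONV rate of about 23%.

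Arm odds ratios, all adjusted for recorded risk:

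| Direct P6 effect | Nominal deviation | No drug term | Planned drug | Administered prophylaxis | Any drug incl. rescue |
|---|---|---|---|---|---|
| none | 0 | 1.001 | 1.001 | 1.001 | 1.001 |
| none | 0.10 | 1.028 | 1.028 | 1.016 | 1.083 |
| none | 0.20 | 1.060 | 1.060 | 1.036 | 1.181 |
| none | 0.40 | 1.095 | 1.095 | 1.056 | 1.407 |
| log OR −0.35 | 0 | 0.723 | 0.722 | 0.722 | 0.727 |
| log OR −0.35 | 0.20 | 0.757 | 0.757 | 0.741 | 0.847 |
| log OR −0.35 | 0.40 | 0.792 | 0.793 | 0.767 | 1.018 |

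A nominal deviation of 0.20 among the 50% with a planned drug affects roughly 0.20 × 0.50 = 10% of the P6 arm. Each log odds ratio has a simulation standard error of about √(4/(400,000 × 0.23 × 0.77)) = 0.0075. Columns within a row use the same patients, so differences between them are tighter.

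Adjusting for the plan reproduces the arm effect without a drug term, to within 0.001, in every row. Adjusting for administered prophylaxis moves it. At 0.20 with no direct effect, the move on the risk scale at a 25% baseline is about 0.25 × 0.75 × ln(1.060/1.036) = 0.4 percentage points.

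**2. Prophylaxis only: upper guide by hand.** If a fraction f of P6 patients get one planned drug fewer and each drug prevents a proportion r of PONV, the part of the arm difference that runs through the drugs is about f × r × 25 points, or f × r/(1 − r) × 20 points.

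- f = 10%: 0.10 × 0.20 × 25 = 0.5 points, up to 0.10 × (0.30/0.70) × 20 = 0.9 points.
- f = 20%: twice this, 1.0 to 1.7 points, against the 5-point target.

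This is the whole indirect path. In the simulation, the administered-drug model removes only part of it.

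**3. Rescue pooled with prophylaxis.** The last column applies. At 0.20 the odds ratio is 1.18 against 1.06 for the plan with no direct effect, and 0.847 against 0.757 under benefit. With no deviation there is almost no distortion.

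**4. Rescue as a separate predictor.** Rescued patients are then predicted perfectly and add nothing on the arm effect. Suppose half of the cases are rescued.

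- Control: 375.75 cases, 187.9 not rescued, 1315 patients left, 14.3%.
- P6: 300.6 cases, 150.3 not rescued, 1353 patients left, 11.1%.
- The log odds ratio is ln(1.333) = 0.288 with or without the rescued patients.
- Standard error, all patients: √(1/375.75 + 1/1127.25 + 1/300.6 + 1/1202.4) = 0.0878. Power is Φ(0.288/0.0878 − 1.96) = 91%.
- Standard error, rescued patients removed: √(1/187.9 + 1/1127.25 + 1/150.3 + 1/1202.4) = 0.117. Power is Φ(0.288/0.117 − 1.96) = 69%.
- With 40% to 70% rescued, power is 76% to 50%.

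This is lost power, not bias. The 91% differs from the article's stated 80% because 1503 per arm gives about 90% by Fisher's exact test; that is a separate matter.

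**The case against.** The strongest reply is that the sentence sits under additional analyses. The trial's main question is answered by the randomised comparison of PONV incidence, for which the sample size was calculated with Fisher's exact test and which is analysed by intention to treat. A reader might infer from this point that the main result is biased. It is not, and that part of the reply stands in full.

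The safeguards are also real: two signatures, administration according to the plan, and a recorded reason for each departure. If adherence is complete, planned and administered prophylaxis coincide and nothing changes.

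It is tempting to state the endpoint overlap as a fact. The article does not support that. It often links administration to prophylaxis, and it names rescue medication separately in *Data management {19}*. The PACU section and {18b} use the looser wording, so the term is ambiguous, no more. Nor do the two weaknesses attach to the same drugs: staff who know the arm give the intraoperative drugs, whereas overlap could come only from postoperative drugs, and PACU nurses are blinded {17a}. A reader might also take the plan to have been collected as a covariate. Its stated purpose is only to fix prophylaxis independently of randomisation, although that is what makes it suitable.

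Finally, one may argue that adjusting for administered drugs targets a direct effect of P6. In the simulation it came closer to the true direct odds ratio of 1.00 than adjusting for the plan did (1.04 against 1.06). But it recovered neither the direct effect nor the total effect, because unrecorded risk drives both drug use and PONV. The article does not name a direct effect as its target.

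**Conclusion.** The point holds for the additional regression only. As worded, it conditions on a post-allocation variable that staff aware of the arm can influence, while a pre-allocation counterpart is already in the dataset. It also leaves open a reading in which the predictor contains part of the endpoint, which includes "or the need for any antiemetic medication during the observation period".

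The size cannot be fixed from the article. For prophylaxis alone it is zero without deviation and small at modest deviation: about 0.4 points in the simulation, with 0.5 to 0.9 points as a rough upper guide, when about 10% of the P6 arm lose a planned drug. It is large only if rescue drugs enter, either as bias when they are pooled with prophylaxis and deviation differs by arm, or as lost power when they are coded separately. The fall from 91% to 69% needs that unstated reading and an assumed rescue rate of 50%. It should not be quoted as a property of the planned analysis.

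**What to change.** In {20b}:

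1. Replace administered antiemetic medication by the self-committed prophylaxis recorded before allocation, as covariate and subgroup factor.
2. Test group-by-planned-prophylaxis and group-by-preoperative-risk interactions.
3. State that postoperative rescue antiemetics are excluded from the predictors.
4. Report administered drugs and deviations from plan by arm, descriptively.
5. Describe any drug effects on PONV as risk-adjusted associations.

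The cost is a change of wording. The plan is already on the form and in the dataset, so no new data are needed and the sample size does not change.

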**Methods:**

The primary objective of the P6NV study is to determine whether intraoperative acustimulation (acupuncture or acupressure) at the point P6 provides additional benefit when applied along with customary prophylactic intravenous antiemetics administered according to the local standard operating procedures (SOP). The primary endpoint is the incidence and severity of PONV within the first 24 h postoperatively reported with a validated postoperative nausea and vomiting intensity scale. The patient-reported outcome of perioperative quality of life (using the PPP33-questionnaire) and the detection of antiemetic-related side effects as well as the severity of PONV (via a standardised questionnaire) are secondary study objectives. P6NV is a national, multicentre, randomised, prospective, patient- and examiner-blinded interventional study and will be performed on 3500 adult patients with ASA classification I–III undergoing elective surgery under general anaesthesia and hospitalised for at least 24 h. Participating anaesthesiologists commit themselves to administer customised conventional antiemetic prophylaxis according to the local SOP by signing a statement before randomisation. The intervention group receives bilateral acupuncture or acupressure at P6. The control group receives no intervention. Before extubation, acustimulation is removed.

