### Objectives {7}

We designed this pragmatic clinical trial to provide evidence whether ad hoc implementation of techniques for P6 acustimulation is effective to improve conventional pharmacologic prophylaxis administered on a customary basis in accordance with local standard operating procedures (SOP) in adult inpatients undergoing elective surgery.

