## Discussion

It is generally accepted that PONV can be reduced to a clinically satisfying level by applying a multimodal antiemetic approach. This can be achieved by combining drugs from different pharmacologic classes or adding the latter to a total intravenous anaesthesia technique. So far, there is limited evidence whether P6 stimulation can be integrated into such a multimodal antiemetic concept or if the addition of acustimulation results in a further reduced incidence of PONV [28–36].

This paper describes the methodology and clinical endpoints of a large randomised controlled clinical trial that investigated the use of acustimulation at point P6 in combination with an individually tailored pharmacological antiemetic treatment regarding the incidence of PONV. Emphasis is given to potential biases deriving from the lack of blinding and inhomogeneous administration of antiemetics to the treatment group versus the control group.

Since P6 acustimulation is performed by anaesthesiologists with limited training performing the procedure, this trial will provide information on the use of an ad hoc implementation of these techniques in an anaesthesia department under real clinical practice conditions. Therefore, the anaesthetic administration has not been standardised, and the results will be transferable to the largest possible patient population.

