### Limitations of the study

Our study may be best classified as a patient- and observer-blinded, block-randomised pragmatic clinical trial. Many efforts were focused on documenting the intended prophylaxis of PONV before the allocation to the study group. For blinding purposes, acustimulation is only applied in the intraoperative period. This rather short-term stimulation during anaesthesia may limit the efficacy of the intervention. Additional emetogenic stimulus (e.g. administration of postoperative opioids) occur after termination of the acustimulation further limiting the effect of the P6 stimulation.

The baseline PONV management is not standardised which might cause an imbalance of baseline PONV risk. We address this particular risk by using risk calculation in both trial arms.

P6 stimulation for this study is based on common descriptions and opinions about traditional acustimulation. However, the study’s standardised procedure of P6 stimulation may be considered as insufficient in duration or technique overall. Therefore, the result can only describe this study’s approach of an ad-hoc implementation with a common standard of P6 stimulation rather than the general effectiveness of P6 stimulation.

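### The planned subgroup regression names no group-by-factor term and uses administered, not planned, antiemetics; as worded it is covariate adjustment

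*Protocol article*

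**What the plan says.** Under Methods for additional analyses {20b}, the whole text is: "Logistic regression will be performed for subgroup analysis concerning group assignment, preoperative risk of PONV and administered antiemetic medication and their effects on PONV". It gives no model formula. It names no interaction and rules none out.

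Other sections bear on how this sentence is read:

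- **Aim.** The abstract asks whether P6 "provides additional benefit when applied along with customary prophylactic intravenous antiemetics". Objectives {7} asks whether it "is effective to improve conventional pharmacologic prophylaxis administered on a customary basis". Both describe the average add-on effect.
- **Discussion.** It notes "limited evidence whether P6 stimulation can be integrated into such a multimodal antiemetic concept", and in the same sentence asks whether adding acustimulation lowers the incidence of PONV further.
- **Limitations of the study.** On possible imbalance in baseline PONV risk it says: "We address this particular risk by using risk calculation in both trial arms". That is an adjustment role for risk.
- **Antiemetic medication.** Background prophylaxis may range from none to combinations of several classes, chosen partly by individual risk.
- **Order of events.** The anaesthesiologist and nurse sign the planned prophylaxis before allocation is revealed (Pharmacological antiemetic prophylaxis), and the envelope is opened afterwards (Intervention). Departures from the plan are recorded with reasons (Strategies to improve adherence {11c}).

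**The concern.** A subgroup analysis asks whether the treatment effect varies between kinds of patient. The sentence lists three predictors and their effects on the outcome, which most naturally means three separate effects. A model of that form assumes that P6 has the same odds ratio in a patient given no drug as in one given three, so it cannot test that assumption. A reader could then present an adjusted overall odds ratio as a subgroup result.

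This matters because prophylaxis varies widely by design, and this entry is the only place in the article where variation of the P6 effect with prophylaxis could be examined.

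The choice of administered medication adds a second problem. The anaesthesia team knows the allocation when it carries out the plan, and the Discussion itself lists uneven antiemetic use between the groups as a potential bias. If allocation shifts what is given, then adjusting for it or forming strata on it compares groups that randomisation no longer balances. A variable free of this problem is already recorded.

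**Working it through.** **1. The model as worded and the model needed.**

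- As worded: logit P(PONV) = b0 + b1·group + b2·risk + b3·antiemetics. The P6 log odds ratio is b1 for everyone.
- With product terms b4·group×risk and b5·group×prophylaxis, the P6 log odds ratio is b1 + b4·risk + b5·prophylaxis. A subgroup statement rests on b4 and b5, which the sentence does not name.

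**2. Timing of the prophylaxis variable.** The documented order is: planned prophylaxis signed, envelope opened, prophylaxis carried out at times the team chooses, deviations recorded. The plan precedes knowledge of allocation. What is administered need not.

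**3. The plan's own figure.** None is given for this regression. The inputs below come from Sample size {14}: 25% vs 20%, two-sided 5%, and 1503 patients, read as per arm because 2 × 1750 follows. For that main comparison, the continuity-corrected formula gives 1134 per arm at 80% power and 1504 at 90%. So 1503 does not reproduce at the stated 80%; it matches 90%. That is a separate matter, and 1503 per arm (3006 in all) is used here only as the number of patients.

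**4. What a main-effects model would report.** Assume two equal strata (751.5 per arm each), with 25% to 20% in one and 25% to 25% in the other.

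- Odds ratio in stratum 1: (0.20/0.80)/(0.25/0.75) = 0.75, log −0.2877. In stratum 2: 1, log 0.
- Variance of a log odds = 1/[n·p(1−p)]. At 25%: 1/(751.5 × 0.1875) = 0.00710. At 20%: 1/(751.5 × 0.16) = 0.00832.
- Variance of the log odds ratio: stratum 1, 0.01541; stratum 2, 0.01419.
- Inverse-variance average: −0.2877 × (1/0.01541)/(1/0.01541 + 1/0.01419) ≈ −0.138, a common odds ratio of about 0.87.

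That single figure describes neither stratum.

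**5. Power of a group-by-stratum term.** This is a Wald test on the log ratio of odds ratios.

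- Same scenario: SE = √(0.01541 + 0.01419) = 0.172; z = 0.2877/0.172 = 1.67; power = Φ(1.67 − 1.96) ≈ 39%.
- With a 30/70 split (450.9 and 1052.1 per arm): SE = 0.189; z = 1.52; power ≈ 33%.

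| Assumed PONV, stratum 1 vs stratum 2 | Ratio of odds ratios | Power, N = 3006 | Power, N = 3500 |
|---|---|---|---|
| 25→20% vs 25→25% | 0.75 | 33–39% | 37–44% |
| 40→30% vs 15→15% | 0.64 | 66–69% | 73–75% |
| 25→15% vs 25→25% | 0.53 | 89–95% | 93–97% |

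Ranges cover the 30/70 and 50/50 splits. All strata are assumed; the article gives none. With equal halves the last row averages to the planned 25→20%, but it needs a 40% relative reduction in the half that benefits. The Sample size section takes about 30% from the earlier review and plans on less. The first row, which keeps the trial's own effect within one stratum, is the sober case.

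**6. Risk differences implied by one odds ratio.** A constant 0.75 turns 10% into 7.7% (2.3 points), 25% into 20% (5.0 points) and 40% into 33.3% (6.7 points). These differences follow from the model's assumption and are no evidence that the effect varies. Risk differences by stratum therefore should not come from the main-effects fit.

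**The case against.** The strongest reply is that this is one sentence in a journal article. Product terms and coding are commonly left to a full protocol or analysis plan that is not shown here, and the label itself suggests that variation of the effect was intended. The stated objective is the average add-on effect, which the randomised comparison answers without any interaction. Adjusting for risk is legitimate and is a purpose the Limitations section gives.

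Much of this stands. It bars several stronger readings that a reader might infer:

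- *That the plan excludes interactions and can give only one averaged P6 effect.* The text does not say so. This follows only if the model is fitted as separate effects.
- *That effect modification is an objective.* The Discussion sentence also covers the average add-on effect. The statement that "techniques for P6 stimulation might interfere with the pharmacological measures against PONV and vice versa" describes bias from unequal co-treatment and leads to the self-commitment form. No section sets an objective for high-risk patients or for a multimodal subgroup.
- *That subgroups will be fitted separately and their p-values compared.* The article plans no such thing, so the error rate of that practice is no criticism of it.
- *That an interaction term would settle the question.* Power near 95% needs the large contrast in the last row of the table.

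The reply does not remove two things that the sentence does state: a label that does not fit the analysis as worded, and administered medication as the factor.

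**Conclusion.** The point holds in limited form. As worded, the regression is covariate adjustment carrying the name of subgroup analysis, and it would not show whether the P6 effect differs by risk or by background prophylaxis. Its prophylaxis variable is fixed after allocation is known, although a pre-allocation version is on file.

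The conclusion rests on the natural reading of the sentence as separate effects; an unseen plan may already contain the terms. How far allocation changes administered drugs is not known from the article, only that it can. With assumed strata, a main-effects model could report about 0.87 where the true odds ratios are 0.75 and 1. An interaction term would detect that contrast in only about 33–39% of trials at 3006 patients. The issue is confined to an additional analysis and leaves the primary comparison untouched.

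**What to change.** In Methods for additional analyses {20b}, state that:

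- the logistic regression uses baseline PONV risk and the planned prophylaxis from the self-commitment form in place of administered medication;
- it includes group × risk and group × planned-prophylaxis terms;
- the interaction estimates are reported with confidence intervals, together with the P6 risk difference by stratum, and all of this is labelled exploratory.

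The coding of planned prophylaxis is the sponsor's choice, fixed before unblinding. A simple count is one option, but it treats all listed measures as interchangeable. If no interaction is intended, the entry should be renamed covariate-adjusted analysis.

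The change uses data already collected and needs no extra patients. Its cost is imprecision: modest interactions will usually be inconclusive, and the report should say that a non-significant interaction does not show a uniform effect.
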